## Abstract

**Background:** Psychological trauma has a strong negative impact on the onset, course and prognosis of substance use disorders (SUD). Few trauma-oriented treatment approaches have been trialed, but preliminary evidence exists of the efficacy of Eye Movement Desensitization and Reprocessing (EMDR) therapy in improving clinical symptoms in SUD patients.

**Objective:** To assess if EMDR therapy leads to: (1) reduced substance consumption; (2) an improvement in psychopathological and in trauma-related symptoms; and (3) an improvement in overall functioning. Our hypothesis is that the EMDR group will improve in all variables when compared to the treatment as usual (TAU) group at 6 and 12-months visits.

**Method:** In this multicenter phase II rater-blinded randomized controlled trial, 142 SUD patients with a history of psychological trauma will be randomly assigned to EMDR (*n* = 71) or to TAU (*n* = 71). Patients in the EMDR group will receive 20 psychotherapeutic sessions of 60 min over 6 months. Substance use will be measured using the Timeline Followback Questionnaire, the Dependence Severity Scale and the Visual Analog Scale. Traumatic events will be measured by The Holmes-Rahe Life Stress Inventory, the Childhood Trauma Questionnaire Scale, the Global Assessment of Posttraumatic Stress Questionnaire, the Impact of Event Scale-Revised and the Dissociative Experiences Scale. Clinical symptomatology will be evaluated using the Hamilton Depression Rating Scale, the Young Mania Rating Scale and the Brief Psychiatric Rating Scale. Functionality will be assessed with the Functioning Assessment Short Test. All variables will be measured at baseline, post-treatment and 12 months as follow-up. Primary outcome: to test the efficacy of EMDR therapy in reducing the severity of substance use. The secondary outcomes: to test the efficacy in reducing trauma-related psychological symptoms and psychopathological symptoms and in improving overall functioning in patients with comorbid SUD and a history of psychological trauma.

**Conclusion:** This study will provide evidence of whether EMDR therapy is effective in reducing addiction-related, trauma and clinical symptoms and in improving functionality in patients with SUD and a history of trauma.

**Clinical Trial Registration:** The trial is registered at ClinicalTrials.gov, identifier: NCT03517592.

## Introduction

Substance use disorders (SUD) represent an important social and public health problem due to their negative consequences in terms of delinquency, family disintegration, academic and occupational disengagement, mental illness, transmission of infectious diseases, intoxication, and mortality rates (1). One significant risk factor for problematic alcohol and substance use is the presence of multiple adverse childhood events, as shown by a recent meta-analysis in the Lancet (2). Different studies have found that between 66 and 97.4% of SUD patients have experienced Criterion A traumatic events according to DSM IV criteria (3–7), and the prevalence of post-traumatic stress disorder (PTSD) in inpatients with SUD is estimated to range from 25–51%, two to four times more than general population rates ranging from 1.3 to 12.3% (8). Even adverse events not meeting PTSD Criterion A have an important impact in the course of the disorder because they have been shown to be associated with substance use outcomes (2).

In order to clarify the difference between psychological trauma, PTSD and subthreshold PTSD, we will provide a brief definition of them. Psychological trauma is a term that refers to any life event that causes discomfort to the subject and exceeds an individual's abilities to integrate the emotions involved with the experience (9). The term PTSD refers to, based on DSM-V criteria (10), exposure to actual or threatened death, serious injury, or sexual violence, accompanied by the presence of the following trauma-related symptoms: intrusion, persistent avoidance of stimuli, negative alterations in cognitions and mood and marked alterations in arousal and reactivity. Symptoms must have a duration of more than 1 month and cause clinically significant distress or impairment in the patient's overall functioning, and not be attributable to the physiological effects of a substance or another medical condition (10). Finally, the term subthreshold PTSD should be used when the clinical presentation does not meet all criteria for PTSD diagnosis.

A large study into populations addicted to alcohol and various illicit drugs found that PTSD and subsyndromal PTSD were correlated with addiction severity, a worse disease prognosis, more hospital admissions, poorer response to treatment, shorter periods of abstinence and greater craving (4). These characteristics make this specific population difficult to treat. In addition, trauma is highly prevalent in patients with severe mental disorders (SMDs) such as depression, bipolar disorder or psychosis, where PTSD and SUD are frequently comorbid and negatively influence the course of mental illness (11, 12). In some cases, disease course is worsened by a high prevalence of trauma-related dissociative symptoms (13). These findings suggest psychological trauma should be assessed in SUD and in dual pathology patients and be included as an objective of the treatment plan (12, 14).

Along these lines, even though pharmacological treatment such as selective serotonin reuptake inhibitors, atypical antipsychotics and benzodiazepines have demonstrated a limited efficacy in the treatment of PTSD and psychological trauma, some drugs such as prazosin could be a promising strategy to consider in adjuvant treatment with the psychological approach, given the positive results shown in specific PTSD symptoms as reported the meta-analysis of Berardis et al. (15).

A recent Cochrane review into the efficacy of CBT-based therapies for comorbid SUD and PTSD found that preliminary evidence showed that trauma-focused therapy delivered alongside SUD therapy could improve PTSD symptoms at short- and long-term, and SUD symptoms at long-term, compared to treatment as usual. They concluded that more research is needed on trauma-focused therapies for this population, but that there is very little evidence to support individual therapies not focused on trauma (16).

One leading trauma-focused treatment is Eye Movement Desensitization and Reprocessing (EMDR) therapy, recommended as a first-line PTSD treatment by international bodies such as the American Psychiatric Association (APA) (17) and the World Health Organization (WHO) (18). Initial studies have shown the potential for EMDR to be applied to the SUD population. Until nowadays, there are three published trials in SUD and EMDR: two small randomized controlled trials (RCT) and one non-randomized controlled trial of EMDR vs. treatment as usual (TAU) in patients with SUD (19–21). They have suggested that EMDR, compared to the control group, significantly improves craving (19), depression, anxiety, self-esteem (19, 20), and dissociative symptoms (21), but results must be repeated with larger samples. A large scale RCT is currently underway (22) to determine the efficacy of EMDR in reducing PTSD symptoms in an inpatient sample with comorbid SUD and PTSD or sub-threshold PTSD.

In the current study, we aim to carry out the first large RCT into the impact of EMDR on SUD symptoms in outpatients (with or without comorbid SMDs) with a history of psychological trauma. This is groundbreaking in, firstly, focusing on addiction outcomes instead of PTSD symptoms as a primary outcome and, secondly, in including all patients showing trauma-associated symptoms, even if they do not fulfill PTSD or subsyndromal PTSD criteria.

Additionally, EMDR is an interesting psychotherapeutic tool for this population due to its potential to improve the course of comorbid SMDs, where strong preliminary evidence also shows EMDR to be a promising treatment beyond PTSD (23), such as in bipolar disorder (24), or psychosis (25), as well as in depression (26, 27) and anxiety (28–30). The evidence that EMDR is efficacious in these kind of patients will help facilitate its application in complex real-world settings.

## Methods

This is a multicenter phase II rater-blinded randomized controlled trial, phase II, with two parallel branches, EMDR and TAU, of patients diagnosed with SUD who have a comorbid history of psychological trauma, even if they do not currently meet DSM-V criteria for PTSD. The patients will be matched by site, age, sex, and diagnosis. One group will consist of TAU plus 20 individual 60-min EMDR sessions over a duration of 6 months, while the other group will receive TAU only. Patients will be evaluated at baseline (T0), 3 months (T1: only substance use-related symptoms), post-treatment at 6 months (T2), and at 12 months as follow-up (T3) (see Table 1). Clinical raters carrying out evaluations will be blind to the participants' research condition. Patients will not be blind to treatment as a sham alternative to EMDR therapy is impossible due to its use of bilateral stimulation.

**Table 1 T1:** SPIRIT flow diagram: schedule of enrolment, interventions, and assessments.

	**Study period**				
	**Enrolment**	**Allocation**	**Post-allocation**		**Close-out**
**TIMEPOINT**	***–t_**1**_ & t_**0**_***	**0**	***t_**1**_***	***t_**2**_***	***T_**3**_***
**ENROLMENT**					
Eligibility screen	X				
PRISM	X				
MINI	X				
HDRS	X			X	X
YMRS	X			X	X
BPRS	X			X	X
TLFB	X		X	X	X
SDS	X		X	X	X
EVA	X		X	X	X
CTQ	X				
H-RLSI	X				
EGEP	X			X	X
IES-R	X			X	X
DES	X			X	X
Informed consent	X				
Allocation		X			
**INTERVENTIONS**					
EMDR					
TAU					
**ASSESSMENTS**					
FAST	X			X	X

*PRISM, Psychiatric Research Interview for Substance and Mental Disorders; MINI, Mini-International Neuropsychiatric Interview; HDRS, Hamilton Depression Rating Scale; YMRS, Young's scale for the evaluation of the Mania; BPRS, Brief Scale of Psychiatric Evaluation; TLFB, Timeline Followback; SDS, Dependence severity scale; EVA, Analog visual scale; CTQ, Childhood Trauma Questionnaire; H-RLSI, The Holmes-Rahe Life Stress Inventory; EGEP, Global Assessment of Posttraumatic Stress Questionnaire; IES-R, Scale of the impact of events reviewed; DES, Scale of Dissociative Experiences; EMDR, Eye movement desensitization and reprocessing therapy; TAU, Treatment as usual; FAST, Functioning Assessment Short Test*.

The study has been approved by the Ethic Committees of the Hospital Benito Menni, Germanes Hospitalàries del Sagrat Cor de Jesús (PR-2018-04), and the IMIM, Parc de Salut Mar (2017/7615/I). All participants will sign informed consent prior to enrollment. Details of the trial design can be also gathered from Supplementary Material (Standard Protocol Items: Recommendations for Interventional Trials [SPIRIT] Checklist).

This is a multicenter phase II collaborative project will involve the participation of five different centers from the Barcelona catchment area, Spain: four outpatient addiction clinics pertaining to the Institute of Neuropsychiatry and Addictions (INAD), Parc de Salut Mar, and a fifth pertaining to the Hospital Benito Menni, in Sant Boi de Llobregat. Both institutions involved are centers of reference in mental health treatment and research, facilitating the recruitment and development of the project. EMDR therapists have extensive experience in EMDR protocols and SUD. All participating raters will be trained in the blind-to-treatment application of all clinical assessments.

### Study Outcomes

The primary outcome is to test the efficacy of EMDR therapy in reducing the severity of substance use in patients with comorbid SUD and a history of psychological trauma, irrespective of whether the patient meets DSM-V PTSD criteria. Changes from baseline in the severity of substance use are measured by the Timeline Follow Back (TLFB) (31), the Severity of Dependence Scale (SDS) (32), and the Visual Analog Scale (VAS).

The secondary outcome is to test the efficacy of EMDR in improving trauma-related psychological symptoms, psychopathological symptoms, and the overall functionality in SUD patients with a history of psychological trauma. Changes in psychological trauma and dissociative symptoms are measured using the Global Assessment of Posttraumatic Stress Questionnaire (EGEP-5) (33), the Impact of Event Scale-Revised (IES-R) (34), and the Dissociative Experiences Scale (DES) (35), respectively. The type and severity of traumatic experiences are measured using the Childhood Trauma Questionnaire (CTQ) (36) and The Holmes-Rahe Life Stress Inventory (37). Changes in psychopathological symptoms are measured by the Hamilton Depression Rating Scale (HDRS) (38), Young Mania Rating Scale (YMRS) (39), and the Brief Psychiatric Rating Scale (BPRS) (40). Changes in overall functioning will be measured using the Functioning Assessment Short Test (FAST) (41).

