### Study Participants

The study sample will consist of 142 outpatients fulfilling the criteria of the Diagnostic and Statistical Manual of Mental Disorders, fifth edition (DSM-5), for SUD based on a clinical interview (Psychiatric Research Interview for Substance and Mental Disorders; PRISM) (42) and a review of case notes.

Inclusion criteria are: (1) aged 18–65, (2) outpatient, and (3) presence of one or more traumatic events currently causing trauma-associated symptoms (Impact of Events Scale-Revised, IES-R > 0) and Subjective Disturbance Unit (SUD) > 5, that assesses subjective disturbance in a scale between 0 and 10, but it is not necessary that traumatic events meet DSM-5 criteria for PTSD.

Exclusion criteria are: (1) presence of organic brain diseases, (2) presence of acute suicidal ideation, (3) having received a trauma-focused therapy or attended psychotherapeutic groups for survivors of violence within the last 2 years, or (4) acute episode of comorbid psychiatric disorder.

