In this trial, all patients meeting the inclusion criteria will receive the baseline (T0) assessment. After T0, participants will be assigned to the EMDR or TAU group following a biased coin procedure (46): (1) the first two patients will be randomly allocated to EMDR with *p* = 0.5, (2) the next patient will be allocated as follows: (b1) if one group already includes at least two more patients than the other group, the patient will be randomly allocated to EMDR with *p* = 0.8 is this is the smallest group and with *p* = 0.2 if it is the largest group, (b2) otherwise, we will first simulate that the patient is allocated to EMDR and calculate the sum of the between-group square standardized differences in site, age, sex, diagnosis (dual vs. not dual) and number of substances consumed during the month before the randomization (none. one or more than one), we will then simulate that the patient is allocated to TAU and recalculate the sum, and finally randomly allocate the patient to EMDR with *p* = 0.8 if this was associated to the smallest sum and with *p* = 0.2 if not. For example, if we had already included 10 patients to the EMDR group and 8 patients to the TAU group, the 19th patient would be randomly allocated with *p* = 0.2 for EMDR and *p* = 0.8 for TAU. If he/she was allocated to TAU, for the 20th patient we would calculate the above sum of covariates after simulating that the he/she is allocated to EMDR and after simulating that he/she is allocated to TAU, and if the sum of the EMDR simulation was larger than the sum of the TAU simulation, we would randomly allocate the 20th patient with *p* = 0.2 for EMDR and *p* = 0.8 for TAU. Following this procedure, the final groups should be balanced in size and matched in site, age, sex and diagnosis. All steps of the randomization process will be automatically carried out by an independent researcher in a central location using a computer program.

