Childhood Trauma Questionnaire (CTQ): The CTQ (36), Spanish validation (50), is a self-administered 28-item scale developed as a screening tool for histories of childhood abuse and neglect, with 5 subscales: emotional, physical or sexual abuse, and emotional or physical neglect. A 5-point Likert scale is used for the responses, ranging from “Never True” to “Very Often True.”Global Assessment of Posttraumatic Stress Questionnaire(EGEP-5): The EGEP-5 (51) is a clinical interview for the diagnosis of PTSD, both current and in the past, based on DSM-V criteria. This scale contains three sections: events, symptoms and functioning.The Holmes-Rahe Life Stress Inventory (37); Spanish validation (52): this is a scale assessing the frequency of 43 common stressful life events over the past 12 months, providing a standardized measure of their impact (53). Scores below 150 reflect low levels of stress, scores between 150 and 299 represent a 50% risk of a stress-related illness in the near future and scores above 300 represent an 80% risk (37), although each individual's reactions to stress and coping ability must be considered.Impact of Event Scale-Revised (IES-R): The IES-R (54), Spanish validation (55), is a 22-item self-report measure of subjective distress over the previous 7 days related to a specific stressful life event. Items correspond directly to 14 of the 17 DSM-IV symptoms of PTSD. Items are rated on a 5-point scale ranging from 0 and 4, yielding a total score ranging from 0 to 88, with subscale scores for Intrusion, Avoidance, and Hyperarousal.Dissociative Experiences Scale (DES): The DES (36), Spanish validation (56), is a 28-item self-reported questionnaire measuring a wide range of dissociative experiences, from normal to pathological, with an overall mean score ranging from 0 to 100 (57).

**Table 3 T3:** Measurements to evaluate psychological trauma symptoms.

**Clinical variable**	**Measurement interview/Self-report**	**T0**	**T1**	**T2**	**T3**
		**Baseline**	**Mid-treatment**	**Post-treatment**	**Post-treatment**
				**6 months**	**12 months**
Childhood T	CTQ	x			
PTSD	EGEP	x		x	x
Traumatic events	H-RLSI	x			
Trauma's impact	IES-R	x		x	x
Dissociation	DES	x		x	x

*Childhood T, Childhood trauma; CTQ, Childhood Trauma Questionnaire; PTSD, post-traumatic stress disorder; EGEP, Global Assessment of Posttraumatic Stress Questionnaire; H-RLSI, The Holmes-Rahe Life Stress Inventory; IES-R, Impact Event Scale; DES, Scale of Dissociative Experiences*.

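### Baseline PTSD, which the protocol calls prognostic and diagnoses before allocation, is neither a named balancing factor nor a named covariate, and the pooled effect cannot by itself show benefit in patients without PTSD

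*Protocol article*

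**What the plan says.** **Aim and population.** Study Outcomes sets the primary aim as efficacy on severity of substance use "irrespective of whether the patient meets DSM-V PTSD criteria". Study Participants matches this: patients need current trauma-associated symptoms (IES-R above 0 and a disturbance rating above 5 out of 10), but "it is not necessary that traumatic events meet DSM-5 criteria for PTSD". The Introduction lists as one of two novel features the inclusion of patients "even if they do not fulfill PTSD or subsyndromal PTSD criteria".

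**PTSD as a prognostic factor.** The Introduction reports that in a large study "PTSD and subsyndromal PTSD were correlated with addiction severity, a worse disease prognosis, more hospital admissions, poorer response to treatment"; shorter abstinence and greater craving are also listed. Dependence severity (SDS) and craving (VAS) are among the three primary instruments.

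**PTSD is known in time.** Instruments and Measures says the EGEP-5 "is a clinical interview for the diagnosis of PTSD, both current and in the past", and Tables 1 and 3 schedule it at baseline. Randomization Procedure says: "After T0, participants will be assigned to the EMDR or TAU group following a biased coin procedure".

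**Allocation and analysis.** The biased-coin sum uses "site, age, sex, diagnosis (dual vs. not dual) and number of substances consumed during the month before the randomization". Statistical Analysis names time, treatment, their interaction and a random site effect. It adds that further covariates, which it does not name, will be tried and that significant ones may be kept. None of the seven hypotheses concerns PTSD status.

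**The concern.** The protocol gives its own reason for using a biased coin: unrestricted randomisation can leave a trial of this size unbalanced on known confounders. The Limitations section then relies on matched arms to control heterogeneity. By that reasoning, a factor that the Introduction stresses as prognostic and that is already recorded before allocation is an obvious candidate for the balancing list. It is absent, and adjustment for it depends on a significance screen.

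Two things are at stake. One is some avoidable noise and chance imbalance in the treatment estimate. The other is interpretation. The sample mixes patients with and without PTSD by design, and the analysis described gives one average effect. A reader drawn by the novelty statement could take a positive average as evidence that EMDR helps patients without PTSD, which an average alone cannot show.

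**Working it through.** **Inputs from the protocol**
- 64 evaluable per arm (128 in total), 71 recruited per arm (142), d = 0.5, power 80%, loss about 10% (Computation of Sample Size).
- PTSD prevalence: the Introduction says "the prevalence of post-traumatic stress disorder (PTSD) in inpatients with SUD is estimated to range from 25–51" per cent. It describes inpatients and this trial enrols outpatients, so I use 25%, 38% and 51% as an assumed range.

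**Assumptions of mine:** two-sided alpha 0.05 (not stated; the default of the R function cited), unit SD of change, equal PTSD share in both arms for the precision figures.

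**1. The plan's own figure.** A two-sample t-test with d = 0.5, alpha 0.05 two-sided and power 0.80 gives n = 63.77, so 64 per arm; power at 64 is 80.1%. Allowing for loss, 128 / 0.9 = 142.2, in line with the stated approximate 142. The sample size reproduces, for the overall comparison only.

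**2. Chance imbalance in PTSD.** With 71 per arm and nothing in the sum capturing PTSD, the number of PTSD patients in one arm is hypergeometric (142 patients, K with PTSD, 71 drawn).

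| Prevalence | K of 142 | P(gap ≥ 10 points) | P(gap ≥ 15 points) |
|---|---|---|---|
| 25% | 36 | 18% | 3% |
| 38% | 54 | 23% | 6% |
| 51% | 72 | 24% | 6% |

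Two independent binomials instead give 15–21% and 4–8%, the same picture.

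**3. What a gap does to the estimate.** Shift = gap × prognostic effect of PTSD on the outcome. The protocol gives no size for that effect, so I assume 0.5 to 1 SD:
- 10-point gap: 0.10 × 0.5 = 0.05 SD to 0.10 × 1 = 0.10 SD.
- 15-point gap: 0.15 × 0.5 = 0.075 SD to 0.15 × 1 = 0.15 SD.

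The design effect is 0.5 SD.

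**4. What the average can hide.** Average effect = p × (effect with PTSD) + (1 − p) × (effect without). As an illustration with no source in the protocol, take 1.0 and 0: the average is 0.25 at p = 0.25 and 0.51 at p = 0.51. Only at the top of the range does it reach the design effect of 0.5, but there a positive trial would be compatible with no benefit in patients without PTSD.

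**5. How well the strata could be estimated.** With 64 analysed per arm:
- Half-width of the 95% interval without PTSD = 1.96 × √(2 / (64(1 − p))).
- Half-width for the interaction = 1.96 × √(2 / (64p) + 2 / (64(1 − p))).

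| Prevalence | Per arm with / without PTSD | Half-width without PTSD | Half-width interaction | Power, d = 0.5 without PTSD | Power, interaction 0.5 SD |
|---|---|---|---|---|---|
| 25% | 16.0 / 48.0 | 0.40 SD | 0.80 SD | 68% | 23% |
| 38% | 24.3 / 39.7 | 0.44 SD | 0.71 SD | 60% | 28% |
| 51% | 32.6 / 31.4 | 0.49 SD | 0.69 SD | 50% | 29% |

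Detecting an interaction of 0.5 SD with 80% power would need about 503 to 670 evaluable patients. The trial can describe the effect by PTSD status but cannot settle whether it differs.

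**The case against.** A reader might infer that the primary aim itself goes untested, because it promises efficacy whatever the PTSD status. The documents do not support that. Read with Study Participants and the opening of Methods, the phrase mainly says who is enrolled, and the treatment-by-time contrast tests average efficacy in exactly that population. No hypothesis or objective claims separate benefit in each group, and any trial's average could in principle come from one subgroup. This part of the objection stands.

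It is also too strong to say that PTSD is certainly unbalanced and unused. The factor dual versus not dual may partly capture PTSD; the protocol does not say. Randomisation balances PTSD in expectation, so the test stays valid. The unnamed covariates could include PTSD, and a full covariate or subgroup list is normally left to an analysis plan that is not shown here. I therefore do not count the lack of a subgroup plan as an error. The point rests on what the article does state: a specific list of balancing factors without PTSD, and a significance screen for covariates.

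Two further points stand. The shift from a 10-point gap is small. The Introduction's correlations are for PTSD and subsyndromal PTSD together, so a yes/no PTSD term is a coarse version of the prognostic factor and places subsyndromal patients with the rest.

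**Conclusion.** The point holds as a worthwhile improvement, not as a flaw that undermines the trial. An already collected baseline variable that the protocol itself calls prognostic is left out of the stated balancing list, and its adjustment is left to a significance screen. Under the assumed 25–51% prevalence, a gap of 10 points or more arises in about one trial in four to six (18–24%) and moves the estimate by 0.05–0.10 SD, if the prognostic effect is 0.5–1 SD and dual status captures none of PTSD.

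The pooled result will be a valid average for the mixed population. It should not be presented as efficacy shown both with and without PTSD. Exploratory estimates by PTSD status would inform that question, but with half-widths of about 0.40–0.49 SD for patients without PTSD and 0.69–0.80 SD for the interaction they would not resolve it. The prevalence and the prognostic effect are assumptions and could differ in these outpatients.

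**What to change.** 1. If recruitment has not started, add current PTSD (EGEP-5 at T0, yes/no) as a sixth term in the biased-coin sum.
2. In any case, include it as a prespecified fixed covariate whether or not it is significant. If the baseline value is one of the repeated outcomes, enter PTSD with its interaction with time, since a main effect alone shifts the level and hardly adjusts the change.
3. State whether PTSD counts as a dual diagnosis in the balancing factor.
4. Report the treatment effect with confidence intervals in patients with and without PTSD, and the interaction, all labelled exploratory. Make no formal claim depend on them.
5. Word the conclusion as an average effect in a mixed population.

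Cost: one variable in the allocation program and a few model terms, with no new data collection. Balance on the other five factors becomes slightly looser, and the subgroup intervals will be wide.
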